### Participant timeline {18}

Figure 1 shows the participant’s journey in this research study. Participants will first be assessed for eligibility to join. For eligible participants, informed consent will be sought. After completion of baseline assessment, participants will be randomized into one of two groups (intervention or control). Intervention group participants will attend four face-to-face sessions with the research nurse in the RAMP Knee OA intervention. Control group participants will continue with their usual care. Both groups of participants will complete study assessments at week 16, week 32, and week 52 (Fig. 2).

**Fig. 1 Fig1:**
[figure not shown]
RAMP knee OA diagram

**Fig. 2 Fig2:**
[figure not shown]
The schedule of enrolment, interventions, and assessments

### Sample size {19}

There will be two arms in the study: (i) the intervention group (RAMP-Knee OA); and (ii) the control group (usual care). The sample size will be calculated based on the suggested minimal important clinical difference (MCID) of the WOMAC pain score, which is 0.469 in terms of standardized mean difference between groups [52]. Thus, a sample size of 97 in each arm will have 90% power to detect an effect size of 0.469 in a two-sample *t*-test with alpha set at 0.05 (G* power 3.1.9.7). Assuming a 15% dropout rate, the total sample size is 228, with 114 in each arm.

### Recruitment {20}

Patients will be recruited by PCPs in their usual clinic appointments, which are mostly scheduled every 4 months. Social media platforms are also utilized for the promotion of the research study.

## Assignment of interventions: randomization

### Sequence generation: who will generate the sequence {21a}

The randomization sequence is generated by a trained research associate.

### Sequence generation: type of randomisation {21b}

Randomization will be performed in a 1:1 allocation ratio [53].

### Allocation concealment mechanism {22}

The allocation sequence will be concealed through use of sequentially numbered, opaque, sealed envelopes [54].

### Implementation {23}

The allocation sequence will be concealed from the researcher enrolling and assessing participants.

## Assignment of interventions: blinding

### Who will be blinded {24a}

The research assistant and statistician will be blinded in this study.

### How will be blinding be achieved {24b}

In this open-label study, blinding of physicians, nurses, and participants will not be possible. However, all data collection will be performed by trained research assistants blinded to the allocation status of the patients, and the statistician will analyse data without referring to allocation information, thus ensuring blinding.

### Procedure for unblinding if needed {24c}

Since the participants and the research nurse are not blinded in this study, any emergency and research-related health concerns can be addressed timely and accordingly. Thus, no procedure for unbinding was put in place.

## Data collection and management

### Plans for assessment and collection of outcomes {25a}

Validated questionnaires were used to measure study outcomes. The primary outcome will be the Western Ontario and McMaster Universities Osteoarthritis Index (WOMAC; 5-point Likert) pain at 52 weeks. WOMAC is well-known to be the “gold standard” self-reported measure in KOA trials [19, 41]; a validated Chinese version of the WOMAC, with good internal consistency (Cronbach’s alpha > 0.7) and test–retest reliability (intraclass correlation coefficients > 0.80), will be used in this study [42].

Secondary outcomes include a set of biopsychosocial parameters: Physical function will be measured subjectively by WOMAC function subscale [42] and objectively by the 30-second chair and stand performance test [42, 43]. Lower limb muscle mass will be measured by bioimpedance analysis [44]. Physical activity level will be measured by the Chinese International Physical Activity Questionnaire (Short form) [45]. Self-management efficacy will be measured by Pain-Self Efficacy questionnaire [46]. Generalized Anxiety Disorder-7 (GAD-7) and Patient Health Questionnaire-9 (PHQ-9) will be used to measure anxiety and depression, respectively [47, 48]. Insomnia will be measured by the 7-item Insomnia Severity Ind ex (ISI) [49], and loneliness will be measured by the 6-item De Jong Gierveld Loneliness Scale [50, 51]. EuroQuol-5D-5L (EQ-5D-5L) questionnaire will be used to measure health-related quality of life [51].

Other outcomes, including analgesics prescriptions, can be accurately recorded in the electronic medical records, but their consumption, along with over-the-counter drugs, will be logged using medication logs. To maintain a comprehensive record, patients will be provided with medication diaries to note down details such as the name, dosage, frequency, and any specific instructions for each analgesic they take. During regular assessment timepoints, patients will be asked to complete questionnaires that utilize the Timeline Followback method to inquire about their medication usage in the past 14 days. This method involves presenting patients with a calendar and having them retrospectively recall their intake of analgesics over a 14-day period [20].

Cost-effectiveness: cost-effectiveness will be analyzed if the intervention is effective in reducing WOMAC pain score. Quality-adjusted life years (QALYs) of the participants will be assessed by EQ-5D-5L, which is also one of our outcomes. The EQ-5D-5L health state classification instrument has five dimensions: mobility, self-care, usual activities, pain/discomfort, and anxiety/depression. Each dimension has five levels to indicate the severity of the problem in that dimension. The Hong Kong reference value sets will be used to covert EQ-5D-5L health status to the utility weight. Individuals’ QALY will be calculated by using the area under the curve approach. Self-reported data on health service utilization in the past three months will be collected at 0 months and 12 months; this will include hospitalization (frequency and days), visits to GOPCs, specialist out-patient clinics (SOPCs), and the emergency departments. The information on health service use in the public health system will be supplemented by records in the Hospital Authority electronic medical system. The cost of this program such as costs directly related to setup, administration, clinical management, and exercise courses will be recorded. But additional costs related to evaluation and research will not be included.

### Plans to promote participant retention and complete follow-up {25b}

The study provides HKD$400 to each participant as a study incentive. A cash coupon of HKD $100 will be issued to each participant upon completion of each study assessment. This measure promotes participant retention.

### Data management {26}

Data will be double-entered into an electronic database.

### Confidentiality {33}

All collected personal data will be used for research purposes only. Personal data will be handled only by trained research personnel, and confidential data will be stored in an encrypted database.

## Statistical methods

### Statistical methods for primary and secondary outcomes {27a}

Baseline characteristics of the two groups will be compared using the independent samples *t*-test or Mann-Whitney test for continuous variables and chi-square test for categorical variables. Tests of intervention effects on both primary and secondary outcomes at different points will be conducted using Analysis of Covariance (ANCOVA), adjusting for baseline values. All analyses will be conducted using the R statistical program [52].

### Who will be included in each analysis {27b}

All randomized participants (i.e., intervention and control group participants) will be included in the analysis.

### How missing data will be handled in the analysis {27c}

If missing data is present, we will use linear mixed models, which is the approach to use for intention-to-treat analysis in longitudinal clinical trials with missing values [55]. Imputation of missing values before the mixed model analyses is not recommended [56].

### Methods for additional analyses (e.g., subgroup analyses) {27d}

Secondary analyses include adjustments for potential confounders, such as the use of cointerventions, and exploration of the interaction effect of treatment and the potential moderators. These will all be conducted using the R statistical program.

### Interim analyses {28b}

This is a funded study, and progress is reported to the funder at designated time points. Hence, no stopping guidelines were determined for an undesirable interim analysis result. The research assistant and statistician will have access to the interim analysis results.

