### Composition of the data monitoring committee, its role and reporting structure {28a}

A data monitoring committee that is composed of a clinician, a board-certified physiotherapist, and a data scientist is formed for data quality assurance, monitoring, and reporting.

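### Interim results go to the research assistant and the statistician, the only two roles declared blinded, with no statement that the results are pooled or arm-masked

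*Protocol article*

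**What the plan says.** Three parts of the protocol article bear on this point.

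- **Blinding.** Who will be blinded {24a} states: "The research assistant and statistician will be blinded in this study". How will be blinding be achieved {24b} rules out the other roles: "In this open-label study, blinding of physicians, nurses, and participants will not be possible". It then gives the safeguard in two parts. The first concerns assessment of outcomes: "all data collection will be performed by trained research assistants blinded to the allocation status of the patients". The second concerns the analysis, where the article says that "the statistician will analyse data without referring to allocation information, thus ensuring blinding".
- **Interim results.** Interim analyses {28b} mentions progress reports to the funder, concludes that "no stopping guidelines were determined for an undesirable interim analysis result", and ends: "The research assistant and statistician will have access to the interim analysis results".
- **Monitoring body.** The section on the data monitoring committee {28a} says that "A data monitoring committee that is composed of a clinician, a board-certified physiotherapist, and a data scientist is formed", with tasks covering data quality, monitoring and reporting. It is not named as a recipient of interim results.

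**The concern.** In an open-label trial, keeping outcome assessors and the analyst blind is the only blinding that remains. The access rule in {28b} hands interim results to exactly those two roles and attaches no condition to what they may see.

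With by-arm results, a research assistant would carry an expectation about the treatment effect into later assessments. Participants know their arm and may reveal it, so that expectation could be matched to an individual. The 30-second chair-stand test is the most exposed outcome, since performance depends on effort and so on how the test is conducted. The statistician would know the trend before the final analysis. Neither role's knowledge can be withdrawn once given.

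**Working it through.** No figure in the plan is at stake, so the check sets the sections side by side.

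1. **Who is blinded.** {24a} lists the research assistant and the statistician. {24b} says that physicians, nurses and participants cannot be blinded. The set of blinded roles is therefore exactly these two.
2. **Who receives interim results.** {28b} names the research assistant and the statistician, and no one else. The two sets are identical.
3. **What the recipients do.** By {24b}, research assistants perform all data collection. Outcomes {16} puts the full set of outcomes at baseline and at 16, 32 and 52 weeks, including the chair-stand test. The statistician runs the analysis.
4. **What the interim results contain.** {28b} gives no endpoint, comparison, timing or number of looks, and does not mention pooling or masked codes. Its wording about an undesirable result and stopping guidelines fits a between-arm comparison better than a recruitment update. That is an inference.
5. **What decision the access serves.** {28b} says that no stopping guideline was set, and no other use is given. Progress reporting to a funder does not in itself need results by arm.
6. **Whether another recipient exists.** {28a} describes a data monitoring committee, so a body that could hold comparative results is already in place.
7. **Which assessments could be affected.** Trial status gives recruitment from 1 April 2024 to 12 May 2025 and the last visit on 12 May 2026. Adding 52 weeks (364 days) to 1 April 2024 gives 31 March 2025, so primary-endpoint visits fall between about then and 12 May 2026. Any look before the last visit leaves some assessments still to come. No look is dated, so their number cannot be derived.

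Steps 1, 2, 3, 5 and 6 rest on the text. The consequence depends on step 4: if the results are by arm, the access rule conflicts in effect with the blinding rule; if they are pooled, {28b} omits the one qualification that would make it compatible.

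**The case against.** The best case for the plan is that {24b} defines blinding as not knowing patients' allocation and as analysing without allocation information. Group-level results reveal no individual's arm, and {24b} makes no exception for interim work. The two sections could then be read together as access to pooled or code-masked output, and {28b} does introduce the topic through progress reports. Part of this stands: the results do not unblind any patient by themselves, and masked codes could protect the statistician. It does not settle the matter, because no such limit is stated and no reason is given for an outcome assessor to see interim outcome results at all.

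It is also fair that the primary outcome, WOMAC pain, is self-reported by participants who already know their arm. Any additional bias from an assessor's knowledge of a trend may be small beside that. An article may also leave the committee's reporting lines to a fuller document, so its absence from {28b} is supporting evidence only.

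A reader might infer four stronger conclusions that the documents do not support:

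- **That blinding is broken outright.** Aggregate results do not disclose allocation, and a by-arm look is suggested but not stated.
- **That the trial loses all protection against bias.** Randomisation, sealed opaque envelopes and concealment from enrolling and assessing staff remain ({21b}, {22}, {23}).
- **That the type I error is inflated.** That would need interim efficacy tests and action on them; {28b} describes neither.
- **That the statistician could choose between ANCOVA and a mixed model after seeing the trend.** Section {27c} makes the presence of missing data the trigger for the mixed model.

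**Conclusion.** The point holds as a conflict between a stated access rule and a stated blinding rule. It is not a complaint about missing detail: {28b} positively grants access to the two blinded roles, without qualification. If the results are by arm, this undermines the assessor and analyst blinding, and no stated decision benefits.

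The conclusion assumes that the role titles in {24a}, {24b} and {28b} refer to the same staff (the article draws no distinction) and, for its consequence, that the interim output compares arms. The possible bias has no derivable size. It would bear most on assessor-dependent measures such as the chair-stand test and less clearly on self-reported pain. The sections need to be reconciled because the correction is cheap and disclosure is irreversible.

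**What to change.** Replace the last sentence of {28b} with a statement along these lines:

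- Research assistants receive no interim outcome results.
- The trial statistician sees no results by identified arm before database lock.
- Reports to the funder contain only pooled recruitment, retention and data-completeness figures.
- Any comparative look goes only to the existing data monitoring committee.

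If the interim output was only ever meant to be pooled progress data, saying so in {28b} removes most of the difficulty. If output by arm has already been released, record what it contained, when, and to which roles, so that the final report can describe it.

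The cost is a change of wording and a restriction on access. No additional participants, visits or data are needed. Only if a comparative look is wanted must someone other than the blinded statistician prepare it, or the trial statistician do so under masked arm codes.

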### Protocol and statistical analysis plan {5}

Once published, the protocol will be available online. The de-identified data with statistical codes can be obtained from the corresponding author upon reasonable request.

## Oversight and monitoring

### Composition of the coordinating centre and trial steering committee {3d}

The study coordinating center (SCC) is composed of the principal investigator (physician), a research nurse, and the research team members. They are responsible for the conduct of the research study, discussion of study progress, and safety monitoring.

### Composition of the data monitoring committee, its role and reporting structure {28a}

A data monitoring committee that is composed of a clinician, a board-certified physiotherapist, and a data scientist is formed for data quality assurance, monitoring, and reporting.

### Frequency and plans for auditing trial conduct {29}

To monitor and ensure the quality assurance, the SCC will meet weekly to discuss the trial process and any problems encountered during the trial.

### Protocol amendments {31}

There are currently no amendments made to the study protocol. Any amendments required will be officially submitted to the Joint-CUHK-NTEC clinical research ethics committee for approval.

### Dissemination policy {8}

The results of this RCT will be disseminated through presentations at public lectures, scientific institutions, and meetings as well as through peer-reviewed scientific articles.

## Discussion

This protocol describes the rationale and implementation of the RAMP knee OA program in Hong Kong Primary Care setting. The intervention program designed is based on the validated framework and follow the OARSI 2019 treatment algorithm. It includes risk-stratified care planning, self-management support and scheduled health assessments in Hong Kong. The implementation of this study will address the 1 practice-evidence-gap for CCM in Hong Kong and provide a reference for the management plan of patients with knee OA with personalized care chronic knee OA.

## Trial status

The study protocol was approved by the Joint Chinese University of Hong Kong – New Territories East Cluster Clinical Research Ethics Committee on 5 December 2023. The identifier of the approved protocol is version 1 on 11 October 2023. Recruitment began in 1 April 2024 and completed in 12 May 2025. The last patient visit is expected on 12 May 2026.

## Data Availability

The de-identified data with statistical codes and the relevant results in this study will be shared through academic conferences and scientific papers. The datasets can be obtained from the corresponding author upon reasonable request.

## Abbreviations

RAMP: Risk Assessment and Management Program
OA: Osteoarthritis
CCM: Chronic care model
RAMP-Knee OA: Risk Assessment and Management Program on Knee Osteoarthritis
WOMAC: Western Ontario and McMaster Universities Osteoarthritis Index
GAD-7: Generalized Anxiety Disorder-7
PHQ-9: Patient Health Questionna`ire-9
PCPs: Primary care physicians
GOPCs: General outpatient clinics
TIDieR: Template for Intervention description and replication
OARSI: Osteoarthritis Research Society International
BMI: Body mass index
ACSM: American College of Sports Medicine
WHO: World Health Organization
RN: Registered nurse
CMS: Clinical Management System
ISI: Insomnia Severity Index
EQ-5D-5L: EuroQuol-5D-5L
QALYs: Quality-adjusted life years
SOPCs: Specialist outpatient clinics
MCID: Minimal clinically important difference
ANCOVA: Analysis of covariance
SCC: Study coordinating center
